### Participant timeline {13}

The schedule of events for each participant enrolled in this study is presented in Fig. 4. *Enrollment − t*_*1*_*:* Obtain informed consent. Review medical history and medications to determine eligibility based on inclusion/exclusion criteria. Perform medical and neurological examinations needed to determine eligibility based on inclusion/exclusion criteria. Schedule study visits for participants who are eligible and available for the duration of the study. Provide participants with specific instructions needed to prepare for their first study visit, including but not limited to clothing prior to the study. *Baseline visit t*_*1*_*:* Record vital signs. Perform a Lokomat familiarization session. Perform clinical evaluation tests. *Baseline visit t*_*2*_*:* Record vital signs. Record MEPs at rest and during stepping with Lokomat settings obtained from the familiarization session. Provide to the participant the TMS side-effect questionnaire. Record adverse events as reported by participants or observed by investigators. *Baseline visit t*_*3*_*:* Record vital signs. Perform electrophysiological recordings (soleus H-reflex rate-dependent depression and reciprocal inhibition, control, and conditioned soleus H-reflex during BWS-assisted stepping). Record adverse events as reported by participants or observed by investigators. *Intervention visits 4–43:* Administer the assigned transspinal stimulation-locomotor training intervention. Reassess transspinal stimulation threshold and locomotor EMG activity at study Intervention visits *t*_*15*_ and *t*_*30*_. *Final study visits t*_*44*_* and t*_*45*_: Perform clinical evaluation tests and electrophysiological recordings as described in Baseline visits.

**Fig. 4 Fig4:**
[figure not shown]
Standard Protocol Items Recommendations for Interventional Trials (SPIRIT) figure indicating the procedures for each participant that occur at each visit. Each participant comes at least 45 times to the lab receiving a total of 40 treatment sessions

### Sample size {14}

Our study is powered to establish and detect a significant effect size across the 3 groups between pre- and post-intervention. We performed statistical analysis of the preliminary data utilizing G*Power-3 software [88, 89]. The sample size was calculated to obtain a power larger than 0.8.

*Aim 1:* Determine if priming locomotor training with transspinal stimulation increases MEP amplitudes and promotes appropriate MEP amplitude modulation during stepping. The TA MEPmax amplitudes recorded in 10 healthy subjects while at rest were compared before and after 10 sessions of transspinal stimulation delivered with subjects lying supine (difference between means: 148.05, pooled standard deviation: 206.8, d = 0.71). To predict sample size at a power of 0.80 at α = 0.05 using repeated measures, within-between interaction ANOVA across 3 groups, 24 total subjects are needed. We will enroll 45 subjects, so we will be adequately powered even if subjects drop out at a higher than expected 20% rate. This sample size is based on results from healthy control subjects and not from SCI subjects.

*Aim 2*: Determine if priming locomotor training with transspinal stimulation restores spinal inhibition, reduces neurophysiological hyperreflexia, and re-establishes H-reflex modulation during stepping. The soleus H-reflex rate-dependent depression in 6 persons with SCI was recorded at 1.0 Hz from the left leg and compared before and after 15 sessions of transspinal stimulation. Based on the soleus H-reflex recorded at 1.0 Hz before and after transspinal stimulation (difference in means of pre versus post: 25.28, pooled standard deviation: 28.92), the effect size was 0.87. To predict sample size at a power of 0.80 at α = 0.05 using a one-way ANOVA across 3 groups, 18 total subjects are needed. We will enroll 45 subjects, so we will be adequately powered even if subjects drop out at a higher than expected 20% rate.

The soleus H-reflex amplitude during assisted stepping in 11 persons with motor incomplete SCI (AIS C-D) recorded from the right leg was compared before and after locomotor training [26]. Based on the amplitude of the soleus H-reflex at mid-stance before and after training (difference in means of pre versus post: 13.67, pooled standard deviation: 17.4), the effect size was 0.79. To predict sample size at a power of 0.80 at α = 0.05 using a one-way ANOVA across 3 groups, 21 total subjects are needed. We will enroll 45 subjects, so we will be adequately powered even if subjects drop out at a higher than expected 20% rate.

Limb coordination relies on the strength of reciprocal inhibition between antagonistic muscles. We used data from a study performed by our group that examined short-latency inhibition from ankle flexor afferents onto ankle extensor motoneurons at rest in 13 persons with AIS C-D SCI before and after locomotor training [28]. Based on the amplitude of the conditioned H-reflex at the conditioning-test interval of 2 ms before and after training (difference in mean of pre versus post: 15.04, pooled standard deviation: 17.21), the effect size was 0.874. To predict sample size at a power of 0.80 at α = 0.05 using a one-way ANOVA across 3 groups, 18 total subjects are needed. We will enroll 45 subjects, so we will be adequately powered even if subjects drop out at a higher than expected 20% rate. Please note that the established power was based on data from SCI subjects who received either transspinal stimulation or locomotor training separately and not combined.

*Aim 3*: Determine if priming locomotor training with high-frequency transspinal stimulation improves limb coordination and the ability to stand and walk. These are secondary measures, and the study is not powered based on these outcomes.

Collectively, an average of 6 to 8 subjects per group is needed to establish significant differences for primary outcomes before and after transspinal stimulation or locomotor training. By enrolling 15 participants per group, the study will be robustly over-powered to detect these differences despite a projected possible 20% dropout rate, sporadic missing data values, or lower-than-expected observed effect sizes.

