Our *specific objective 2* determines if priming locomotor training with transspinal stimulation evokes appropriate neuromodulation of spinal locomotor networks, as reflected by restored spinal inhibition, reduced neurophysiological hyperreflexia, and re-established phase-dependent soleus H-reflex modulation during stepping. We hypothesize that active but not sham transspinal stimulation delivered during standing (1) restores soleus H-reflex rate-dependent depression, (2) increases the depth of reciprocal inhibition between ankle extensor and flexor muscles, and (3) improves soleus H-reflex phase-dependent modulation towards a more physiological pattern during stepping. We further hypothesize that rate-dependent soleus H-reflex depression and soleus H-reflex modulation during assisted stepping recovers more in the transspinal-standing group than in the transspinal-supine group.

Our *specific objective 3* determines if priming locomotor training with transspinal stimulation improves the ability to stand and walk. Comparing locomotor electromyography (EMG) activity patterns before and after therapy will measure reorganized motoneuron activity and return of reciprocal activation between antagonistic muscles supporting intralimb and interlimb coordination. We hypothesize that the number of motor modules increases in the transspinal-standing group, and that antagonistic muscles show more reciprocal inhibition during stepping.

Our *specific objective 4* establishes clinically functional gains in motor and autonomic function. Improvements in walking ability are assessed with the 10-m test, 2-min test; improvements in balance ability are assessed with the BESTtest. Improvements in bowel, bladder, and sexual function are assessed with questionnaires. Clinical outcomes will be correlated with neurophysiological outcomes to identify predictors of recovery that can be based both on electrophysiological biomarkers and clinical assessment outcomes.

Upon conclusion, this clinical trial will indicate that priming locomotor training with transspinal stimulation improves the ability to stand and walk by facilitation and better synchronization of spinal locomotor neuronal networks and reflex circuits subserving standing and walking. This finding will support that transspinal stimulation works in parallel and not antagonistic to exercise, and can constitute a new standard of care for people with chronic SCI.

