## Statistical methods

### Statistical methods for primary and secondary outcomes {20a}

For each dependent variable (primary and/or secondary outcome), descriptive statistics including frequencies and percentages for categorical variables and means and percentile distributions for continuous variables to examine the distribution of outcomes and describe the study population are performed.

We will group each dependent variable based on the time of testing (before and after the intervention) and the subject group (2 experimental, 1 sham). A two-way mixed analysis of variance (ANOVA) along with Bonferroni post hoc* t-*tests [93] at 2 3 levels (2: time, 3: groups) to test the main and interaction effects among subject groups and time will be performed separately for each outcome. Furthermore, repeated measures analysis of covariance (ANCOVA) will be performed for each outcome separately with gender, age, level of SCI, and clinically evaluated baseline walking function as separate covariates. Outcomes will not be analyzed based on SCI severity because the ISNCSCI scale does not correlate with improvements in walking ability [3], while age is considered one of the predictors of ambulation in SCI [94].

Mixed regression methods and analysis of slope and threshold of correlation will be used to establish the relationship between the ability to stand and walk, quality of life, and changes in primary outcomes (neurophysiological biomarkers). We will use an identity or log link based on the data distribution.

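### Aim 2 is sized for the three-group omnibus ANOVA, but its standing-versus-supine hypothesis rests on Bonferroni pairwise t-tests for which no power is given

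*Protocol article*

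**What the plan says.** Sample size {14} sizes Aim 2 on three outcomes. For rate-dependent depression it gives "difference in means of pre versus post: 25.28, pooled standard deviation: 28.92), the effect size was 0.87", and concludes, "using a one-way ANOVA across 3 groups, 18 total subjects are needed". For the H-reflex at mid-stance it gives "difference in means of pre versus post: 13.67, pooled standard deviation: 17.4), the effect size was 0.79", and concludes, "using a one-way ANOVA across 3 groups, 21 total subjects are needed". Reciprocal inhibition (15.04 over 17.21, effect size 0.874) again leads to 18. The section ends: "By enrolling 15 participants per group, the study will be robustly over-powered to detect these differences", allowing for 20% dropout.

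Objectives {7}, specific objective 2, sets pairwise hypotheses. Active stimulation in standing should work where sham does not, and H-reflex depression and modulation during stepping "recovers more in the transspinal-standing group than in the transspinal-supine group".

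Statistical methods {20a} plans, for each outcome, "A two-way mixed analysis of variance (ANOVA) along with Bonferroni post hoc" t-tests over two times and three groups. It names no other pairwise test.

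**The concern.** An omnibus F test asks whether any of the three arms differs. It cannot say whether standing is better than supine, which is the trial's posture question. In the plan as written, that answer must come from the post hoc t-tests at a Bonferroni level, and power for the F test does not carry over to them. The trial could report a significant overall result and still be unlikely to settle the posture hypothesis, while its readers have been told that the sample is more than large enough. Part of the loss comes from a post hoc rule that a three-arm design does not need.

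**Working it through.** **Inputs.** From Sample size {14}: alpha 0.05, target power 0.80, effect sizes 0.87, 0.79 and 0.874, 15 per arm. With 20% dropout, 15 × 0.8 = 12 per arm (36 in total). Allocation is equal (Trial design {8}). Assumptions of this check: two-sided t-tests on change, pooled error with 3n − 3 degrees of freedom, and three Bonferroni pairs, so 0.05/3 = 0.0167 each.

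**Step 1: reproduce the plan.** Use the noncentral F with three groups and noncentrality f²N. Entering the stated values as Cohen's f:
- f = 0.87: power 0.855 at N = 18 (0.759 at 15)
- f = 0.79: power 0.854 at N = 21 (0.777 at 18)
- f = 0.874: power 0.858 at N = 18 (0.763 at 15)

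So 18, 21 and 18 are omnibus sizes with the stated values used as f. At N = 45 the same test has more than 99% power.

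**Step 2: turn f into a standing–supine gap.** For f to imply a pairwise gap, a pattern of means is needed, and the plan gives none.
- Supine midway: the standing–sham range is f√6, so the gap is f√6/2. This is 0.79 × 1.225 = 0.97 SD up to 0.874 × 1.225 = 1.07 SD.
- Supine equal to sham: the gap is 3f/√2, which is 1.68 to 1.85 SD.

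**Step 3: the d reading.** 25.28/28.92 = 0.874, 13.67/17.4 = 0.786 and 15.04/17.21 = 0.874. Each is a pre-post difference over an SD, which is d and not f. If that d is the whole standing–supine gap, the gap is 0.79 to 0.874 SD, taking the stated SD as the SD of change.

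**Step 4: pairwise power.** Use the noncentral t with noncentrality gap × √(n/2). Example: 0.968 × √7.5 = 2.65 against a critical value of about 2.49 gives 57%.

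The closed-test figures come from simulation with normal change scores. A pair counts as rejected when the omnibus F is significant at 5% and the pair is significant at 5%.

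| Reading | Gap (SD) | Bonferroni, 15/arm | Bonferroni, 12/arm | Closed, 15/arm | Closed, 12/arm |
|---|---|---|---|---|---|
| f, supine midway | 0.97–1.07 | 57–67% | 45–55% | 74–82% | 63–72% |
| f, supine equals sham | 1.68–1.85 | 98–99% | 94–97% | over 99% | 97–99% |
| d is the full gap, supine equals sham | 0.79–0.874 | 38–47% | 29–37% | 48–57%* | 38–46%* |

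*For d = 0.79 and 0.87.

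**Step 5: sensitivity.** On the f reading at 15 per arm, Bonferroni power is 90–95% if supine is a quarter of the way from sham to standing and 12–15% at three quarters. On the d reading, if the stated SD is a raw SD, power at 15 per arm is 18–22% at pre-post correlation 0 and 71–81% at 0.75.

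**Step 6: validity of the closed test.** With two time points the group-by-time F is a one-way ANOVA on change. With three arms, if any two pairwise nulls hold then all three means are equal, so the closed family contains only the global null and the single pairs. Simulated familywise error was 0.050 under the global null, and the null pair was rejected in 0.050 of trials when one arm differed. The F gate removed a Bonferroni rejection of standing versus supine in at most about 0.2% of trials with a true effect.

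**The case against.** The protocol does not say in so many words that it is powered for the posture contrast. The differences it calls over-powered refer back to changes before and after treatment, and each Aim 2 calculation openly names a one-way ANOVA. Bonferroni is valid and prespecified. This is fair, and it means the fault is a claim whose reach is not limited plus a missing figure, not a false statement about standing versus supine. It does not remove the problem, because the posture hypothesis is explicit and the sample-size section offers nothing else to support it.

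A reader might infer that standing versus supine simply has 45–67% power with 45 participants. The documents do not support that. The 45% belongs to 36 completers, and the whole range needs a supine arm exactly midway, which the plan does not state. Specific objective 1 expects supine stimulation not to induce phase-dependent MEP modulation, a pattern close to supine equalling sham for that outcome. Specific objective 2 says only that standing recovers more.

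A reader might also apply Bonferroni to all 15 pairs of the six group-by-time cells, which would lower power further. The text does not give the number of comparisons, and an analysis plan may fix it. Three pairs is the lenient reading and the one used here.

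Finally, power computed with d taken as f is too favourable, so the f-based rows should not be copied into the protocol as the corrected power.

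**Conclusion.** The point holds in limited form. The 18, 21 and 18 are omnibus sizes, objective 2 contains a pairwise posture hypothesis, and no power is given for it. That power cannot be fixed from the documents because it depends on where supine falls. With three Bonferroni pairs it is below 80% when supine is midway on the f reading, and also when d is the full gap and the stated SD is that of change. It is above 90% when f is taken at face value and supine equals sham. That the post hoc t-tests decide the hypothesis is an inference, though the plan names no other pairwise test.

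The d reading also touches the omnibus claim. With f = d/2, omnibus power at 45 is 62–72%. The closed test is a real gain in every pattern checked, but it does not bring the contrast to 80% in all of them.

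**What to change.** 1. In Statistical methods {20a}, replace the Bonferroni post hoc t-tests by: *For each outcome the group-by-time interaction is tested at 5%. If it is significant, the three between-arm differences in change are each tested at 5% (closed procedure for three groups).* This controls the familywise error within each outcome.
2. In Sample size {14}, limit the statements of adequate power and over-powering to the omnibus test, and only so far as they survive when the effect size is treated as d. Add power for standing versus sham and standing versus supine at 36 and 45 participants under the closed procedure. Give the assumed pattern of the three means, and treat the effect size as a standardised difference, not as f.

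**Cost.** No new participants or data are needed. No pair can be declared when the interaction is not significant, which in simulation mattered for at most about 0.2% of trials for this contrast. Recruitment began in March 2021, so this is an amendment, to be approved by the route in the amendments section {25} before unblinding. The restated power for the posture contrast will probably look less favourable than the present wording.

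### The Aim 2 sample sizes (18, 21, 18) come from entering Cohen's d as the ANOVA effect size f, so they and the over-powered claim are unsupported for comparisons between arms

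*Protocol article*

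**What the plan says.** Sample size {14} sets the target: "The sample size was calculated to obtain a power larger than 0.8". It names the software: "We performed statistical analysis of the preliminary data utilizing G*Power-3 software". Aim 2 then has three calculations, each at alpha 0.05 and power 0.80.

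- H-reflex rate-dependent depression, 6 persons with SCI before and after stimulation: "difference in means of pre versus post: 25.28, pooled standard deviation: 28.92), the effect size was 0.87". The conclusion is "using a one-way ANOVA across 3 groups, 18 total subjects are needed".
- Soleus H-reflex at mid-stance during stepping, 11 persons before and after locomotor training: difference 13.67, pooled SD 17.4, effect size 0.79. The conclusion is "using a one-way ANOVA across 3 groups, 21 total subjects are needed".
- Reciprocal inhibition at rest, 13 persons before and after locomotor training: difference 15.04, pooled SD 17.21, effect size 0.874, again 18 in total.

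The section closes by putting the need at 6 to 8 participants per group and says that, with 15 per group, "the study will be robustly over-powered to detect these differences despite a projected possible 20% dropout rate". The planned analysis in Statistical methods {20a} is "A two-way mixed analysis of variance (ANOVA"), with two time points and three groups, followed by Bonferroni post hoc tests.

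**The concern.** Cohen's d and Cohen's f are different quantities. d is a difference between two means divided by an SD. f, which the one-way ANOVA routine takes, is the SD of the group means divided by the within-group SD. For three arms, f is less than half of the d between the extreme arms. Using d in place of f therefore more than doubles the assumed effect and cuts the required sample size to between about a quarter and a third.

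The three outcomes concerned are all listed as primary, and three of the section's four sample-size calculations are affected. The per-group figure and the assurance of ample power despite dropout, missing data and smaller effects rest largely on them. Someone relying on this section would take the comparison between arms to have a wide margin that the calculation does not show.

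**Working it through.** **Inputs.** All come from Sample size {14}, except the three equal arms (Trial design {8}). Alpha is 0.05 and target power 0.80. Planned enrolment is 45 (15 per arm); 20% dropout leaves 45 × 0.8 = 36 (12 per arm). The effect sizes are 25.28/28.92 = 0.874 (stated as 0.87), 13.67/17.4 = 0.786 (stated as 0.79) and 15.04/17.21 = 0.874.

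**Formula.** Power of a one-way ANOVA with three equal groups is the probability that a noncentral F variable with 2 and N − 3 degrees of freedom and noncentrality N × f² exceeds the 5% critical value. N moves in steps of 3.

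**Step 1: reproduce the stated totals by entering the stated effect sizes as f.**

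| f entered | Smallest N with power ≥ 0.80 | Power at that N | Power at N − 3 |
|---|---|---|---|
| 0.87 | 18 | 0.855 | 0.759 |
| 0.79 | 21 | 0.854 | 0.777 |
| 0.874 | 18 | 0.858 | 0.763 |

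All three totals match.

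**Step 2: convert d to f.** Let the extreme arms differ by d.

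- Third mean midway (−d/2, 0, d/2): f = √[(d²/4 + d²/4)/3] = d/√6 = 0.41d, the smallest possible.
- Two means equal (0, 0, d): f = √[(d²/9 + d²/9 + 4d²/9)/3] = d√2/3 = 0.47d, the largest possible.

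Read backwards, f = 0.87 means extreme arms 0.87 × 3/√2 = 1.85 to 0.87 × √6 = 2.13 SD apart.

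**Step 3: repeat the stated one-way ANOVA with the converted f.**

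| d | f | N for 80% power | Power at stated N | Power at 45 | Power at 36 |
|---|---|---|---|---|---|
| 0.87 | 0.355-0.410 | 81-63 | 0.21-0.27 | 0.53-0.66 | 0.43-0.55 |
| 0.79 | 0.323-0.372 | 96-75 | 0.21-0.27 | 0.45-0.57 | 0.36-0.47 |
| 0.874 | 0.357-0.412 | 81-60 | 0.21-0.27 | 0.53-0.66 | 0.43-0.55 |

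**Step 4: the planned group-by-time test.** With two time points, this F test is the one-way ANOVA on change scores. The SD of change is the raw SD × √[2(1 − ρ)], where ρ is the pre-post correlation, so the f from step 2 is divided by √[2(1 − ρ)]. The article gives no ρ, so the values below are assumptions; the ranges span all three d values and both patterns of means.

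| ρ | Power at 45 | Power at 36 |
|---|---|---|
| 0.3 | 0.33-0.51 | 0.27-0.41 |
| 0.5 | 0.45-0.66 | 0.36-0.55 |
| 0.7 | 0.67-0.88 | 0.56-0.78 |
| 0.8 | 0.85-0.97 | 0.75-0.93 |

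At ρ = 0.5 the SD of change equals the raw SD, so that row matches step 3.

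**Step 5: detectable difference between two arms at 80% power** (two-sample t-test on change, in SDs of change).

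| Per arm | Alpha 0.05 | Bonferroni, three pairs |
|---|---|---|
| 15 | 1.06 | 1.25 |
| 12 | 1.20 | 1.41 |

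**The case against.** **A reader might infer that the trial is underpowered.** The document does not support that as a fact. Every quoted d is a change within one group, and the section itself notes that its SCI data come from stimulation or locomotor training given separately. No between-arm effect is documented, so the true power is unknown. The 0.45-0.66 needs the extreme arms to differ by exactly the quoted d and, for the planned test, ρ = 0.5. At ρ = 0.8 the same d gives 0.85 or more with 45 participants. This objection stands, and the powers are given here only as conditional figures.

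**A reader might also call the one-way ANOVA the wrong test.** That is too strong. With two time points it is equivalent to the planned interaction test once it is applied to change scores. What is missing is the SD scale on which the effect is expressed.

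**The over-powered sentence can be read as referring to pre-post change,** since the sentence before it speaks of differences before and after treatment. If d is taken as a standardised paired change, one arm of 15 has power 0.81-0.88, one of 12 has 0.70-0.79, and all arms pooled exceed 0.99 at 36 or 45. The claim is therefore defensible for pooled change. It is not defensible for a single arm or between arms, and this reading does not rescue the stated totals: a paired t-test with 6 or 7 per group has power of only 0.35-0.49. Nor is it the stated calculation, which is an ANOVA across three groups.

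**Aim 1's total of 24 is not part of this point.** It comes out from f = d/2 = 0.355 with ρ = 0.5 in the within-between routine and equally from f = 0.71 in a one-way ANOVA (power 0.833 either way), so it does not show which was entered.

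It is also tempting to say that a null result would be misread as absence of effect. No rule in the article says so.

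**Conclusion.** The error is established. The Aim 2 effect sizes are Cohen's d by the article's own arithmetic, and using them as f gives exactly 18, 21 and 18. Those totals do not follow from the stated inputs and test. If the largest between-arm difference equals the quoted d, the stated ANOVA needs 60 to 96 participants depending on outcome and pattern of means, about three to five times the stated totals (60/18 = 3.3; 96/21 = 4.6).

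The consequence for the trial's real power is conditional. It rests on the assumed between-arm difference, the pattern of arm means, the number of completers and the pre-post correlation. The supportable conclusion is that the three totals, the 6 to 8 per group and the over-powered claim have no valid basis for between-arm comparisons, not that 45 participants are known to be too few.

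**What to change.** Keep 45 participants and rewrite the Aim 2 part of Sample size {14} and its closing paragraph.

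- Remove 18, 21 and 18 and the 6 to 8 per group.
- Drop the over-powered claim, or limit it expressly to pooled pre-post change. Bring the repeated assurances of adequate power in Aim 2 into line.
- Restate power for the group-by-time test (or a baseline-adjusted group effect), converting d to f under a stated pattern of arm means and a stated pre-post correlation with its range, at 45 and at 36 completers.
- State that the quoted d values are within-group changes, and that using them as between-arm differences is an assumption.
- Report the detectable difference between two arms: about 1.06 SD of change with 15 per arm and 1.20 with 12 at unadjusted alpha 0.05, or 1.25 and 1.41 with Bonferroni for three pairs.

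The cost is a rewritten section and a less favourable power statement. No participants are added, and neither the design nor the analysis changes.
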